## Abstract

**Background:**

Early and intensive treatment is important to inducing remission and preventing joint damage in patients with rheumatoid arthritis. While intensive combination therapy (Disease Modifying Anti-rheumatic Drugs and/or biologicals) is the most effective, rheumatologists in daily clinical practice prefer to start with monotherapy methotrexate and bridging corticosteroids. Intensive treatment should be started as soon as the first symptoms manifest, but at this early stage, ACR criteria may not be fulfilled, and there is a danger of over-treatment. We will therefore determine which induction therapy is most effective in the very early stage of persistent arthritis. To overcome over-treatment and under-treatment, the intensity of induction therapy will be based on a prediction model that predicts patients' propensity for persistent arthritis.

**Methods:**

A multicenter stratified randomized single-blind controlled trial is currently being performed in patients 18 years or older with recent-onset arthritis. Eight hundred ten patients are being stratified according to the likelihood of their developing persistent arthritis. In patients with a high probability of persistent arthritis, we will study combination Disease Modifying Antirheumatic Drug therapy compared to monotherapy methotrexate. In patients with an intermediate probability of persistent arthritis, we will study Disease Modifying Antirheumatic Drug of various intensities. In patients with a low probability, we will study non-steroidal anti-inflammatory drugs, hydroxychloroquine and a single dose of corticosteroids. If disease activity is not sufficiently reduced, treatment will be adjusted according to a step-up protocol. If remission is achieved for at least six months, medication will be tapered off. Patients will be followed up every three months over two years.

**Discussion:**

This is the first rheumatological study to base treatment in early arthritis on a prediction rule. Treatment will be stratified according to the probability of persistent arthritis, and different combinations of treatment per stratum will be evaluated. Treatment will be started early, and patients will not need to meet the ACR-criteria for rheumatoid arthritis.

**Trial registration:**

This trial has been registered in Current Controlled Trials with the ISRCTN26791028.

## Background

Rheumatoid arthritis (RA) is a chronic inflammation of the joints that causes structural joint damage, affecting daily physical functioning and often limiting social functioning and work participation. [1-7] Its prevalence in Europe is around 1%.[8] Although its primary cause is unknown, multiple genetic and environment factors seem to be involved.[9] While no cure has been found, combinations of disease-modifying anti-rheumatic drugs (DMARDs) and biologicals have proved very effective in reducing disease activity and radiological progression, especially when given early in the disease course. [10-22]

The studies to have reported this were all performed in patients who fulfilled the ACR criteria of RA. But if the treatment of RA is to be improved, it is necessary to go beyond the ACR criteria, a number of which apply to features of later stages of the disease, and are thus insensitive in early rheumatoid arthritis.[23]

The need for earlier treatment is recognized by the EULAR, who recommend not only that "patients at risk of developing persistent or erosive arthritis should be started with DMARDs as early as possible, even if they do not yet fulfil established classification criteria for inflammatory rheumatological diseases," but also "among the DMARDS, methotrexate is considered to be the anchor drug, and should be used first in patients at risk of developing persistent disease."[24] However, it is unclear which criteria should be used for the early identification of persistent disease.

One way of identifying patients at risk for persistent disease would be by using early arthritis-prediction models[25,26], none of which have yet been used for treatment decisions in daily practice. Visser et al developed a prediction rule with seven factors: 1.) symptom duration at the first visit, 2.) morning stiffness for at least one hour, 3.) arthritis in three or more joints, 4.) bilateral compression pain in the MTP joints, 5.) IgM-RF positivity, 6.) anti-CCP positivity, and 7.) erosions on radiographs of the hands or feet. The odds ratio (OR) of each variable was simplified by substituting the ORs with weighted scores from 0 to 13 points. The range of probabilities to which this translated lay between a 10% probability of developing persistent arthritis when one point was scored, and a 99% probability when 13 points were scored. Greater detail is available in Visser et al.[26]

The main aim of the present study is to determine which prediction-guided treatment strategy is superior in patients with recent-onset arthritis who, on the basis of the Visser Prediction rule, are stratified as having a low, intermediate or high risk of developing persistent arthritis.

## Methods

### Study design

The Treatment in the Rotterdam Early Arthritis Cohort (tREACH) is a multicenter stratified randomized single-blind controlled trial. Patients aged ≥ 18 years with at least one arthritis (symptom duration less than one year) will be invited to participate. After providing written informed consent, eligible patients will be stratified into three groups according to the likelihood (on the basis of the prediction model of Visser described previously) of their progressing to persistent arthritis. Patients in each stratum will be randomized to three treatment strategies (a so-called 3 × 3 design). Variable block randomization will be accomplished by a coordination center by telephone during working hours. Treatment strategy will be predefined for the first year, after which the rheumatologist will be free to prescribe as they see fit. Follow-up will take place every three months over a period of two years.

### Recruitment

Patients are currently being recruited from a large prospective cohort study, the Rotterdam Early Arthritis Cohort (REACH study). This includes patients aged ≥ 16 years who live in the area of Rotterdam and have inflammatory joint complaints whose symptoms they have had for less than one year. The REACH study is being conducted in cooperation with the general practitioners in the region.[3,5]

To be included in the present study, patients should have had at least one arthritis confirmed by a rheumatologist. They will be excluded 1.) if they are were diagnosed with a crystal arthropathy, infectious or post-infectious arthritis, or an autoimmune rheumatic disorder other than RA; 2.) if they have been on DMARD therapy, corticosteroids within the last three months, or on concomitant treatment with any experimental drug; or 3.) if there are any of the following: contra-indications for the initial study medication (history of chronic liver disease; excessive alcohol and drug use; pregnancy or the desire to become pregnant during the study; childbearing potential without adequate contraception; or the following laboratory abnormalities: leucopenia (< 3.0 × 10^9^/l), thrombocytopenia (< 150 × 10^9^/l), ASAT/ALAT > double the upper normal value creatinine level > 150 μmol/l).

### Interventions

The medical interventions evaluated in tREACH include three conventional DMARDs: methotrexate (MTX), sulfasalazine (SSZ) and hydroxychloroquine (HCQ). Since intensive treatment is important early in the disease course, this trial is designed to produce the greatest treatment differences during the first three months of therapy (induction therapy).

In this 3 × 3 design, three treatment strategies will be evaluated per probability stratum:

1. A high-probability group (HP), in which the risk of developing persistent arthritis is >70%

2. An intermediate-probability group (IP), in which this risk lies between 30% and 70%

3. A low-probability group (LP), in which this risk is < 30%

Treatment strategies will be tightly controlled, with patients being examined every three months.[27] The aim of treatment is to reduce disease activity as expressed by the Disease Activity Score (DAS) ≤ 2.4.[28] If initial treatment fails (DAS>2.4), the treatment will be intensified using the next step of the prescribed treatment strategy. If the DAS ≤ 2.4, initial treatment will be continued; if the patient meets the criteria for remission (DAS ≤ 1.6) over three successive visits, it will be tapered off. If there is a discrepancy between the DAS score and the opinion of the rheumatologist, an additional DAS will be performed two weeks later. If the discrepancy persists, the initial DAS will be used.

### Induction therapy

Figures 1, 2 and 3 show the the types, dosages of induction and step-up therapy for the three probability groups.

**Figure 1 F1:**
[figure not shown]
**Medication strategies in the high-probability group**. Dosages: MTX: 25 mg/week oral or subcutaneously. SSZ: 2 grams/day. HCQ: 200 mg twice a day. Single-dose corticosteroids intramuscularly: kenacort 80 mg once intramuscularly, or depomedrol 120 mg once intramuscularly. Prednisone scheme: Week 1–4 15 mg a day. Week 5–6: 10 mg a day. Week 7–8: 5 mg a day. Week: 9–10: 2.5 mg a day. Etanercept: 50 mg once a week subcutaneously. Adalumimab: 40 mg once every two weeks subcutaneously. Rituximab: 1 gram intravenously, repeated after two weeks. Leflunomide: 20 mg once daily.

**Figure 2 F2:**
[figure not shown]
**Medication strategies in the intermediate probability group**. Dosages: see figure 1 legend.

**Figure 3 F3:**
[figure not shown]
**Medication strategies in the low-probability group**. Dosages: see figure 1 legend. NSAID: Naproxen 1000 mg/day.

In the HP group, the three induction therapies are:

• Combination DMARD (MTX, SSZ and HCQ) therapy with single-dose corticosteroids intramuscularly

• Combination DMARD (MTX, SSZ and HCQ) therapy with cumulative high-dose corticosteroids

• MTX with cumulative high-dose corticosteroids

In the high probability group, osteoporosis prophylaxis (risedronate 35 mg once a week; combination of calcium and vitamin D 500/440) will be given to patients who are treated with cumulative high-dose corticosteroids during induction therapy.

In the IP group, the three induction therapies are:

• MTX

• Cumulative high-dose corticosteroids

• HCQ

In the LP group, the three induction therapies are:

• Naproxen

• Single-dose corticosteroids intramuscularly

• HCQ

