### Drug side-effects and concomitant drugs

In the event of side effects or contra-indications for the study medication, patients will be treated with leflunomide 20 mg 1 dd. During follow-up, Non-Steroidal Anti-Inflammatory Drugs (NSAIDs) and intra-articular injections will be allowed. Safety monitoring of treatment will take place according to Dutch guidelines.

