## Statistics

### Sample size

Sample-size calculations were based on the AUC HAQ using primary data from the BeST study[15], where the mean AUC HAQ of the combination therapy was 7.7 (SD 5.5) and the mean AUC HAQ of monotherapy was 10.5 (SD 7.4)

To detect this difference using a significance level of α = 0.05 and a power of 80%, ninety patients are needed in each treatment arm. This number of patients is sufficient to detect a difference of 6.1 AUC DAS and 20% of patients with or without radiographic progression towards baseline (α = 0.05; power 80%).

In total, 810 patients will be needed. Allowing for a participation rate of 80%, 1012 patients will have to be screened, which corresponds with 337 patients in each probability group. With seven hospitals involved, we expect to recruit 34 eligible patients a month.

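### As worded, osteoporosis prophylaxis for the high-dose corticosteroid course covers only the high-probability group, leaving out one intermediate-probability arm that apparently receives the same course

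*Protocol article*

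**What the plan says.** All references are to the protocol article.

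- **The rule.** Methods, Induction therapy, directly after the list of high-probability (HP) arms: "In the high probability group, osteoporosis prophylaxis (risedronate 35 mg once a week; combination of calcium and vitamin D 500/440) will be given". The sentence goes on to name the recipients, described as "patients who are treated with cumulative high-dose corticosteroids during induction therapy". It thus fixes the drugs, the dose, the exposure that triggers it and the group to which it applies.
- **The arms.** The same section gives "cumulative high-dose corticosteroids" to two of the three HP arms, once with triple DMARD therapy and once with methotrexate. The list of intermediate-probability (IP) arms, which follows the rule, has an arm with the same label and no DMARD. The low-probability group has only a single intramuscular dose.
- **The dose.** The Figure 2 legend (IP group) reads "Dosages: see figure 1 legend". The only oral corticosteroid regimen in the Figure 1 legend begins "Prednisone scheme: Week 1–4 15 mg a day" and steps down to 2.5 mg a day by weeks 9 and 10.
- **The arm size.** Statistics, Sample size: "ninety patients are needed in each treatment arm".
- **Other safety text.** The section on side effects and concomitant drugs states: "Safety monitoring of treatment will take place according to Dutch guidelines". It does not mention bone protection.

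**The concern.** The trigger is exposure to a particular corticosteroid course, while the scope is a prognostic stratum, and the two do not coincide. A reader who applies the sentence literally would give a bisphosphonate, calcium and vitamin D to HP patients on the course, and would have no instruction to do so for IP patients on what appears to be the same course.

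What is at stake is consistency of protective care by the sponsor's own rule. The trial's inferences are not at stake: treatments are compared within each stratum, and the IP arm is handled alike for all its patients whichever way the sentence is read.

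**Working it through.** **1. Planned numbers.** The plan's total is reproduced first: 3 strata × 3 arms × 90 = 810, as stated under Sample size. The arm size is used here only as a planned count.

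**2. The corticosteroid course (Figure 1 legend).** Cumulative dose = sum of days × mg per day.

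| Weeks | Days | mg/day | mg |
|---|---|---|---|
| 1–4 | 28 | 15 | 420 |
| 5–6 | 14 | 10 | 140 |
| 7–8 | 14 | 5 | 70 |
| 9–10 | 14 | 2.5 | 35 |
| Total | 70 | | 665 |

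- Mean dose: 665 / 70 = 9.5 mg/day.
- Days at 10 mg or more: 28 + 14 = 42 of 70.
- Dose in the first six weeks: 420 + 140 = 560 mg, and 560 / 665 = 84%.

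**3. Who is inside and outside the rule as worded.**

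| Group | Arms on the course | Planned patients | Covered as worded |
|---|---|---|---|
| HP | 2 of 3 | 2 × 90 = 180 | yes |
| IP | 1 of 3 | 1 × 90 = 90 | no |
| Total | 3 | 270 | 180 |

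Share outside the rule: 90 / 270 = 33%.

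**4. Does other text supply or explain the difference?**

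- *Bone risk.* The strata come from a seven-factor prediction rule described in the Background: symptom duration, morning stiffness, the number of inflamed joints, and "bilateral compression pain in the MTP joints, 5.) IgM-RF positivity, 6.) anti-CCP positivity, and 7.) erosions on radiographs of the hands or feet". Age, sex and bone density are not among them, so the stratum is not a stated proxy for bone risk.
- *Overtreatment.* The Discussion raises this to explain the choice and intensity of induction treatments in the IP group. It says nothing about co-medication in either direction.
- *Guidelines.* The reference to Dutch guidelines concerns safety monitoring. It neither provides prophylaxis in the IP arm nor rules it out.
- *Later exposure.* The rule is tied to induction. The section on treatment failure names no further corticosteroids in either group, so it shows no greater planned exposure in HP.

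No visible text covers the IP arm or gives a reason for leaving it out.

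**The case against.** The strongest reply is that a condensed article is merely silent about the IP arm. The sentence follows the HP list and can be read as a local description of those arms. It does not say that IP patients get nothing, and Figure 2, the full protocol or the guidelines may cover them. The last part stands: unseen material could settle the matter for patients. But the article did not leave prophylaxis to another document. It printed a complete rule and limited it expressly to one group, so the wording is open to correction even if practice is sound.

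A second reply is that the groups differ in more than the label. Both HP arms add DMARDs, while the IP arm is corticosteroids alone, and the risk of persistent arthritis is above 70% in HP against 30% to 70% in IP. That is true, and either could lie behind the restriction, but the article offers neither as the reason and its trigger refers only to the corticosteroid course.

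A reader might also infer that the trial withholds protection the sponsor considered necessary. The text does not support this. It says that prophylaxis is to be given, and states no necessity and no dose or duration threshold. Whether 665 mg over 10 weeks calls for prophylaxis cannot be judged from the documents.

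**Conclusion.** The point holds as an inconsistency in a stated rule, at low severity. As worded, prophylaxis reaches 180 of the 270 patients planned for the course and leaves out the 90 in one IP arm, without a stated reason.

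This rests on one assumption: that the IP arm uses the Figure 1 prednisone scheme. The shared label, the cross-reference and the absence of any other oral scheme make that likely, but Figure 2 is not shown. The Discussion describes the oral course as lasting three months; the 10 weeks used here follow the dosing legend.

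A reader might go further and conclude that IP patients would be harmed, or that the comparisons are biased. Neither follows. The documents give no fracture or bone-loss rate, so no harm can be quantified, and no within-stratum comparison, sample size or power depends on this sentence.

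**What to change.** Change only the scope of the sentence, so that it opens with the high- and intermediate-probability groups instead of the high-probability group alone. Keep the drugs, the doses and the exposure trigger as they are. The sponsor's own trigger then applies to every arm with that exposure, and planned coverage rises from 180 to 270.

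The cost is short-term risedronate plus calcium and vitamin D for about 90 more patients. This is a real downside in a group where the sponsor names overtreatment as a concern, and the documents give no figures to weigh it against the benefit. Sample size, endpoints and analysis stay as they are. If Figure 2 or the full protocol already provides prophylaxis in the IP arm, nothing changes for patients and only this sentence needs correcting.

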### Treatment failure (DAS > 2.4)

If DAS>2.4, the DAS will be measured every three months, and treatment will be intensified by step-up therapy according to the next step of the treatment protocol (figure 1, 2 and 3).

For patients in the HP group step-up therapy will be the combination of MTX and anti-TNF α (Etanercept), if therapy still fails after 3 months patients will be switched to another anti-TNF α (Adalumimab). [29-31] The final step-up will be B-cell depletion (Rituximab).

The initial step-up in the IP group and LP group will be the combination DMARDs (MTX-SSZ-HCQ). If failure persists treatment will be intensified to the combination of MTX and anti-TNF α (Etanercept), and finally to another anti-TNF α (Adalumimab).

### Disease remission (DAS ≤ 1.6)

In all probability, if remission (DAS ≤ 1.6) is achieved over three consecutive visits, a group's medication will be tapered off. Step-down of therapy in patients using the combination of MTX-SSZ-HCQ will start with tapering SSZ in the first three months, followed, if this is successful, by tapering off MTX over three months and finally HCQ will be stopped. If patients using the combination of MTX and anti-TNF α achieve remission, first the anti-TNF will be stopped and, if remission sustained, MTX is finally stopped. Patients achieving remission during B-cell depletion therapy, first of all B-cell depletion will be stopped and if this is successful, MTX will be tapered off.

### Drug side-effects and concomitant drugs

In the event of side effects or contra-indications for the study medication, patients will be treated with leflunomide 20 mg 1 dd. During follow-up, Non-Steroidal Anti-Inflammatory Drugs (NSAIDs) and intra-articular injections will be allowed. Safety monitoring of treatment will take place according to Dutch guidelines.

### Data collection

The primary outcome parameters are functional ability (HAQ), disease activity (DAS), and radiological joint damage (the modified Sharp van der Heijde score (modified SvH)).

The HAQ is a self-report functional status measure assessing eight activities 1.) dressing and grooming, 2.) arising, 3.) eating, 4.) walking, 5.) hygiene, 6.) reaching, 7.) gripping, and 8.) common daily activities.[32] For each of these categories, patients report the amount of difficulty they have performing two or three specific activities. The HAQ score is 0–3 with a minimal clinically important difference of 0.22.

The DAS includes the Ritchie articular index, the 44 swollen joint count, the Erythrocyte Sedimentation Rate, and a general health assessment on a VAS.[28] The DAS ranges between 0 and 10.

The modified SvH score will be used to determine the extent of joint damage.[33] Single-emulsion radiographs of the hands (posteroanterior view) and feet (anteroposterior view) will be obtained and digitized for blinded reading. Two independent blinded readers will score the radiographs of each patient by assessing joint erosions (0–5 scale) and joint-space narrowing (0–4 scale) per joint.

The HAQ and DAS will be scored every three months, and X-ray data will be collected every six months over two years of follow-up.

Secondary outcome parameters will include 1.) WHO/ILAR and EULAR Core-set measurements for clinical trials [34,35], 2.) self-assessed disease activity (RADAI)[36], and 3.) Quality of life on the basis of the SF-36 and the Euroqol [37,38].

Using self-reported questionnaires and chart data, additional data will be collected on direct and indirect healthcare costs, and adverse and seriously adverse events.

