### Analysis

Baseline characteristics will be presented with descriptive statistics. Number, mean, standard deviation, and minimum and maximum values will be used for continuous data; and absolute and relative frequencies will be used for categorical data.

Data on the primary outcomes HAQ and DAS will be analyzed per strata of probability (HP, IP and LP) over time using the AUC (area under the curve), which is an appropriate method for detecting therapy difference early in the follow-up period. Analysis will be performed using intention-to-treat analysis and per-protocol analysis. Data on radiological progression will be analyzed using the non-parametric Mann-Whitney U test. All data will be analyzed using STATA 9.0 and R.

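### Three unranked primary outcomes and three arms per stratum, each outcome sized at the full 5%, with no rule for which result names the superior strategy

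*Protocol article*

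**What the plan says.** All places are in the protocol article.

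- **Aim (end of Background):** "The main aim of the present study is to determine which prediction-guided treatment strategy is superior in patients with recent-onset arthritis". The question is asked within risk strata.
- **Study design:** "Patients in each stratum will be randomized to three treatment strategies". There are three strata, so nine arms.
- **Data collection:** "The primary outcome parameters are functional ability (HAQ), disease activity (DAS), and radiological joint damage". No order of importance is given.
- **Sample size:** for AUC HAQ, "To detect this difference using a significance level of α = 0.05 and a power of 80%, ninety patients are needed in each treatment arm". The same 90 per arm is then said to suffice for an AUC DAS difference of 6.1 and for "20% of patients with or without radiographic progression towards baseline (α = 0.05; power 80". Each outcome therefore receives the whole 5%.
- **Analysis:** HAQ and DAS are analysed per stratum through the area under the curve, with no test named. Radiological progression is analysed with the Mann-Whitney U test. Further, "Analysis will be performed using intention-to-treat analysis and per-protocol analysis".
- **Discussion:** two specific objectives are set for the high-probability stratum, methotrexate monotherapy against combination DMARDs and one intramuscular corticosteroid dose against the oral course. No contrasts are singled out for the other two strata.

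**The concern.** Three outcomes and three pairs of arms give up to nine ways to find a difference in a stratum. The protocol does not say which outcome decides, which contrasts count, or what follows when HAQ, DAS and radiographs disagree. A strategy could be called superior on whichever comparison reaches 5%, and the chance of that when the arms are equivalent is well above 5%.

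The sample size is part of the problem. The arms were sized as if each stratum were one two-arm comparison at an unadjusted 5%. A correction added later in an analysis plan would control the error but would lower the power the protocol states. That is why the point belongs in the protocol and is more than a detail left for later.

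**Working it through.** **1. Reproduce the 90 per arm.** Inputs from the Sample size section: means 7.7 and 10.5, SDs 5.5 and 7.4, α = 0.05, power 80%. Sidedness is not stated; two-sided is assumed.

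- Difference: 10.5 − 7.7 = 2.8.
- Root-mean-square SD: √[(5.5² + 7.4²)/2] = √42.505 = 6.52.
- n per arm = 2 × [6.52 × (1.960 + 0.842)/2.8]² = 85.1, so 86. The t-test version gives 87. One-sided would give 68.
- Dividing 85.1 by 0.955, the efficiency of the Mann-Whitney test under normality, gives 89.1, so 90. This is a possible route to the stated figure, not one the article gives.
- t-test power at 90 per arm is 81.7%.

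The stated 90 thus fits an unadjusted, two-sided, two-arm comparison at 5%. It leaves almost no room for adjustment: t-test power at 90 per arm falls to 68% at α/3 and 53% at α/9.

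**2. Chance of at least one false positive per stratum.** Treating nine tests as independent gives 1 − 0.95⁹ = 37.0%. This is too high, because contrasts share arms and outcomes are correlated. I therefore use simulation: three arms, three outcomes, no true difference on any of them, two-sided 5% z-tests, 2,000,000 replicates. The article gives no correlation between outcomes, so it is varied as an assumption.

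| Assumed correlation | Nine tests (3 outcomes × 3 pairs) | Six tests (3 outcomes × 2 contrasts, as in the high-probability objectives) | Overall three-arm test at 5% before the pairs, for each outcome |
|---|---|---|---|
| 0 | 32.3% | 24.8% | 14.2% |
| 0.3 | 30.9% | 23.8% | 13.7% |
| 0.5 | 28.6% | 22.0% | 12.7% |
| 0.7 | 24.9% | 19.2% | 11.1% |
| 0.9 | 19.5% | 14.8% | not run |

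One outcome with three unadjusted pairwise tests already gives 12.2%.

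**3. Check the remedy.** For AUC HAQ alone, an overall test at 5% followed by pairwise tests at 5% only if it is significant gives a family-wise error of 5.0% per stratum when no arm differs. With three groups this is a closed procedure, so the 5% also holds when only two arms are equal.

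Power to pass the overall test and also detect the 2.8 pair, at 90 per arm (F-test, then Welch t-test):

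- third arm equal to the better arm: about 79–80%;
- third arm midway: about 72%;
- third arm equal to the worse arm: about 76%.

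All three are above the 68% from dividing α by three.

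**The case against.** The strongest reply is that the article never says all nine comparisons are tested at 5%. The α of 0.05 appears only in the Sample size section, and the Analysis section names no test, level or list of contrasts for HAQ or DAS. A condensed article may leave the multiplicity method to a fuller document. This stands: the nine-test figure is conditional and cannot be presented as the trial's error rate. It does not remove the point, because the unranked outcomes, the full 5% for each and the two-arm sizing are all written down, and a later correction would break the stated power.

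Four stronger readings are tempting but not supported:

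- **That the Mann-Whitney test settles how every outcome is tested.** It is named for radiographs only. It suggests two-group comparisons there, but does not show that all pairs are tested, that no overall test comes first, or how HAQ and DAS are compared.
- **That 25–32% applies to every stratum.** The Discussion names two objectives for the high-probability stratum, so the lower range fits there if only those are tested.
- **That error should be totalled over the three strata.** They are separate populations with different treatments and separate conclusions, so no joint correction is called for.
- **That intention-to-treat must be declared the sole primary set.** The missing ranking against per-protocol is largely an analysis-plan detail. The high-probability objectives ask whether one option works as well as another, and for that kind of question demoting the per-protocol analysis is not obviously right.

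**Conclusion.** The point holds in conditional form. The protocol fixes three unranked primary outcomes and three arms per stratum, sizes each outcome at an unadjusted two-arm 5%, and sets a superiority aim without a decision rule.

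The chance of a false claim per stratum is up to about 25–32% if all nine comparisons are tested unadjusted, and about 19.5% at a correlation of 0.9. It is about 19–25% in the high-probability stratum with its two named contrasts, and about 11–14% with an overall test first for each outcome. These figures assume two-sided tests, no true difference on any outcome, one significant result being enough to name a winner, and correlations of 0 to 0.7 that the article does not supply. The absence of a ranking and of a rule is certain; the percentages depend on those assumptions.

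**What to change.** 1. **Data collection and Analysis:** make AUC HAQ the single deciding outcome in each stratum, or place it first in a fixed hierarchy with AUC DAS and then the modified SvH score after it.
2. **Analysis:** compare the three arms with an overall test at 5%, and test pairs at 5% only if that is significant.
3. **Sample size:** state that power for the 2.8 difference at 90 per arm is then about 72–80%, depending on where the third arm lies, in place of a flat 80%.

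This should be settled before any unblinded comparison. A split of α across outcomes would also control the error, but at a larger loss of power.

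**Cost:** with 90 per arm kept, the changes are to wording and to the power statement. DAS and SvH can no longer name a superior strategy by themselves, and the declared power is somewhat less favourable. Holding 80% wherever the third arm lies would need more patients.
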